#### Inclusion criteria

We will include only individuals who have received a clinical diagnosis of idiopathic Parkinson’s disease from a board-certified neurologist, in accordance with the UK Brain Bank criteria [38], and who have independent locomotion.

#### Exclusion criteria

We will exclude individuals who meet any of the following criteria: (i) have another neurological disease in addition to Parkinson’s disease; (ii) be above stage III of the adapted Hoehn & Yahr (H&Y) scale [39]; (iii) have characteristics that make the tDCS application unsafe, such as metallic skull implant or epilepsy; (iv) any orthopedic and/or vision problems that impossibilities to comply with the experimental protocol and; (v) cognitive decline (score below 24 points on the Mini-Mental State Examination—MMSE) [40]. PwPD who change their medications during the study will also be excluded.

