## Abstract

Gait impairments negatively affect the quality of life of people with Parkinson’s disease (PwPD). Aerobic exercise (AE) is an alternative to alleviate these impairments and its combination with transcranial direct current stimulation (tDCS) has demonstrated synergistic effects. However, the effect of multitarget tDCS application (i.e., motor, and prefrontal cortices simultaneously) combined with physical exercise on gait impairments is still little known. Thus, the proposed randomized clinical trial will verify the acute effects of AE combined with tDCS applied on motor and prefrontal cortices separately and simultaneously on gait (spatial-temporal and cortical activity parameters) in PwPD. Twenty-four PwPD in Hoehn & Yahr stages I-III will be recruited for this crossover study. PwPD will practice AE on treadmill simultaneously with the application of anodal tDCS during four intervention sessions on different days (∼ one week of interval). Active tDCS will be applied to the primary motor cortex, prefrontal cortex, and both areas simultaneously (multitarget), with an intensity of 2 mA for 20 min. For sham, the stimulation will remain at 2 mA for 10 s. The AE will last a total of 30 min, consisting of warm-up, main part (20 min with application of tDCS), and recovery. Exercise intensity will be controlled by heart rate. Spatial-temporal and cortical activity parameters will be acquired before and after each session during overground walking, walking with obstacle avoidance, and walking with a cognitive dual task at self-preferred velocity. An accelerometer will be positioned on the fifth lumbar vertebra to obtain the spatial-temporal parameters (i.e., step length, duration, velocity, and swing phase duration). Prefrontal cortex activity will be recorded from a portable functional near-infrared spectroscopy system and oxygenated and deoxygenated hemoglobin concentrations will be analyzed. Two-way ANOVAs with repeated measures for stimulation and moment will be performed. The findings of the study may contribute to improving gait in PwPD. Trial registration: Brazilian Clinical Trials Registry (RBR-738zkp7).

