## Materials and method

### Study design and setting

A randomized, crossover, double-blind, sham-controlled clinical trial will be conducted at the Posture and Gait Studies Laboratory (LEPLO) of São Paulo State University (Unesp), Institute of Biosciences, Rio Claro. This study protocol adheres to the Standard Protocol Items: Recommendations for Interventional Trials (SPIRIT) checklist (S1 Checklist) [37]. The project was approved by the research ethics committee of the same University (CAAE: 54476421.1.0000.5465) and is registered on the Brazilian Clinical Trials Registry platform (RBR-738zkp7) with the Universal Trial Number (UTN) code U1111–1277-3248. Other documents on ethical appraisal can be found in the supporting information (S1–S4 Files). PwDP will visit the laboratory for non-consecutive five days, with screening assessments and treadmill familiarization conducted during the first visit. During the remaining four visits (minimum of one week apart), participants will undergo pre- and post-assessments (gait and cortical activity) and a session of AE combined with anodal tDCS (applied on M1, PFC, multitarget, or sham condition). All experimental procedures will be performed at the same time of the day for each PwPD and during the ON state of Parkinson’s disease medication. Fig 1 shows a SPIRIT diagram for the timeline of procedures.

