### Participants

#### Sample recruitment and selection

This study will employ the convenience sampling technique, selecting, and recruiting PwPD from the community-dwelling. The sample size was calculated in G*Power software version 3.1, based on data from Fernandez-Lago colleagues [35]. The primary outcome and statistical tests used were gait velocity and Two-way ANOVAs with repeated measures (within factors), respectively (alpha = 0.05; beta = 0.08; ηp^2^ = 0.43). The sample size analysis indicates a minimum of 16 PwPD is required for this study. Considering the potential for sample loss, we will invite 24 PwPD to participate in the clinical trial through personal and/or telephone contact (from November 10^th^, 2023, to March 31^st^, 2024). In case we have a positive reply, a member of the research team will explain the study’s objectives, risks, benefits, and ethical implications. If participants consent to participate in the study, they will be asked to sign two copies of an informed consent form (one for themselves and the other for the member of the research team).

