### Statistical analysis

Statistical analysis will be conducted using SPSS 25.0 software (International Business Machines Corporation, Armonk, New York, USA), with a significance level set at *p* < 0.05. Clinical, cognitive, and demographic characteristics will be summarized using means and standard deviations or medians and quartiles (25–75) based on the normality of data distribution. The side effects of tDCS will be analyzed with Friedman’s ANOVA. Means and standard deviations will be calculated for primary, second, and intervention outcomes (treadmill velocity and total distance covered, SPE, and percentage of HRmax). Two-way ANOVA with repeated measures for stimulation (M1 x multitarget x PFC x sham) and moment (pre and post) will be employed to analyze gait parameters and activity cortical in each walking condition separately (usual, obstacle avoidance, and dual task). The Mauchly test will be used to check sphericity, and the Greenhouse-Geisser correction will be adopted if necessary. In the case of interaction between factors, Bonferroni post hoc tests with adjusted significance levels will be utilized to identify differences. Finally, for each combination of AE and tDCS, the Standardized Response Mean will be calculated as the effect size of the intervention, considering the mean difference between moments (post—pre) divided by the standard deviation of change.

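### The complete-case repeated-measures ANOVA and the exclusion for medication change discard usable crossover sessions, by an amount that the protocol does not allow to be sized

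*Protocol article*

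**What the plan says.** The Statistical analysis section of the protocol article fixes both software and model: "Statistical analysis will be conducted using SPSS 25.0 software", and "Two-way ANOVA with repeated measures for stimulation (M1 x multitarget x PFC x sham) and moment (pre and post) will be employed". The ANOVA is run separately for each walking condition, with Mauchly's test and, if needed, the Greenhouse-Geisser correction. Under Study design and setting, "During the remaining four visits (minimum of one week apart), participants will undergo pre- and post-assessments", so each participant has 4 × 2 = 8 cells per outcome and walking condition.

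The Exclusion criteria section ends with a rule that acts after entry: "PwPD who change their medications during the study will also be excluded". It does not say what happens to sessions completed before the change.

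On numbers, Sample recruitment and selection says "The sample size analysis indicates a minimum of 16 PwPD is required for this study" and then "Considering the potential for sample loss, we will invite 24 PwPD to participate in the clinical trial". The abstract puts it differently: "Twenty-four PwPD in Hoehn & Yahr stages I-III will be recruited for this crossover study". No loss rate and no cause of loss is given in either place.

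**The concern.** The classical repeated-measures ANOVA in SPSS deletes listwise. A participant with any of the eight cells empty drops out of that ANOVA altogether. Someone who completes three of the four sessions then contributes nothing to that outcome, although each session carries its own pre and post assessment and can be interpreted on its own.

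The medication rule has a similar effect. A change between, say, the third and fourth sessions does not spoil the first three, but the text makes no provision for keeping them.

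Two things are at stake. The first is precision in a trial of about 24 people. The second is balance. The analysed set is selected on events after randomisation, and the planned model has only stimulation and moment as factors. Counterbalancing of order is therefore the only stated protection against period effects. Removing whole participants can unbalance the orders, with nothing in the model to adjust for it.

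A lesser matter is whether 24 counts people invited or people recruited, since this decides how much loss the margin over 16 can absorb.

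**Working it through.** **The plan's own figures.** The minimum is 16 and the planned number is 24. The gap is 8/24 = 33.3%, or equivalently 16/(1 − 1/3) = 24. This percentage is derived here; the protocol does not state it. The 16 is taken as given, because the G*Power option, number of measurements, correlation and sphericity value behind it are not reported.

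**Inputs.** N = 24 participants, 4 sessions each, so 24 × 4 = 96 sessions (Abstract; Study design and setting). The chance q that a session is missing and the chance m that a participant changes medication are not in the document. Both are assumptions, shown over a range.

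**Complete cases, independent session loss, m = 0.**
- Participants kept: 24 × (1 − q)^4
- Sessions that exist: 96 × (1 − q)
- Sessions the ANOVA uses: 96 × (1 − q)^4

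| q | Participants kept | Sessions that exist | Sessions used | Usable sessions discarded |
|---|---|---|---|---|
| 2% | 24 × 0.922 = 22.1 | 94.08 (98%) | 88.55 | 5.5 |
| 5% | 24 × 0.815 = 19.5 | 91.20 (95%) | 78.19 | 13.0 |
| 10% | 24 × 0.656 = 15.7 | 86.40 (90%) | 62.99 | 23.4 |

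The share of existing sessions discarded is 1 − (1 − q)^3, that is 5.9%, 14.3% and 27.1%.

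**Chance of at least 16 complete cases** (binomial, 24 participants, m = 0): 0.98 at q = 5% and 0.55 at q = 10%.

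**Adding medication changes.** If a fraction m of participants is removed with all their sessions, the number kept is 24 × (1 − m) × (1 − q)^4. With m = 10% this is 19.9, 17.6 and 14.2 for q = 2%, 5% and 10%. The chance of at least 16 is then 0.83 at q = 5% and 0.29 at q = 10%.

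**Sensitivity to independence.** If missing sessions all fell on the same few people, who missed every session, the number kept would be 24 × (1 − q) = 23.5, 22.8 and 21.6. The ANOVA would then discard nothing that exists. The table therefore describes scattered losses. Losses clustered within people cost less at the same q.

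**Invited or recruited.** All figures above start from 24 participants who enter. If 24 is the number invited, refusals and screening failures come off first. A 10% failure to enter multiplies the numbers by 0.90, exactly as m = 10% does: at q = 5%, 24 × 0.90 × 0.815 = 17.6 with no medication change at all.

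**The case against.** The strongest reply is that the protocol already carries a margin. At 5% session loss 19.5 of 24 remain, above 16, and the chance of reaching 16 is 0.98. It is still 0.83 if one participant in ten also changes medication. That stands: at modest loss the plan's own target is safe.

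A second reply is that missing-data handling is commonly left to an analysis plan, and none is shown. It is true that the article states no complete-case rule in words. But it does name the software, the factorial within-subject ANOVA and the sphericity tests, and deletion of incomplete participants follows from that choice. The point concerns a stated method.

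Third, the medication rule has a visible rationale. Assessments are made in the ON state, and a change of medication would disturb within-person contrasts. That supports setting aside sessions after a change, but not those before it. Since the text does not explicitly delete earlier sessions, the point can only be put as what the rule appears to do. It is also separate from the ANOVA.

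A reader might go further and infer that the trial expects to lose a third of its participants and that the analysis itself causes most of this. The document supports neither. The 33% is only the gap between 24 and 16, and no cause is named. Attributing it to listwise deletion needs about 9.6% of sessions missing (1 − (2/3)^(1/4)), a rate with no source in the protocol.

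Nor does the argument extend to counting each fNIRS recording as a further chance of losing the participant and comparing the result with 16. Three trials per condition and averaging over four channels per hemisphere make an empty cell less likely. Missing fNIRS data do not remove gait data, and 16 was derived for gait velocity.

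**Conclusion.** The concern holds in a limited form. Followed as written, the plan discards completed sessions of anyone with an incomplete set, and apparently those of anyone who changes medication. It does so in a small crossover whose model does not adjust for period. The loss cannot be sized from the document. Under independent session loss of 2% to 10% it ranges from 22.1 to 15.7 complete cases of 24, and it is smaller if losses cluster in the same people. Only towards the upper end of that range, or with medication changes or failed recruitment added, does the stated minimum of 16 come under threat.

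With complete data the planned ANOVA is valid. The case for change is that a better method is available at little cost. The difference between inviting and recruiting 24 is a real but secondary inconsistency.

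**What to change.** - **Model.** Analyse all randomised participants with a linear mixed model for each outcome and walking condition, using every completed session. Include fixed effects for stimulation, moment, their interaction and period, and a random effect for participant. A random effect for visit within participant is a natural addition, because pre and post share a day. Fit by REML with Kenward-Roger or Satterthwaite degrees of freedom, since plain maximum likelihood tends to understate variances with about 24 people. The planned Bonferroni comparisons can be kept.
- **Analysis set.** State that sessions completed before a medication change stay in the analysis, and add a sensitivity analysis that includes any later sessions collected. This concerns which data are analysed, not how medication is managed. Setting aside later sessions is still selection on an event after randomisation, so the change reduces that problem without removing it.
- **Numbers.** Reconcile the sample-size section with the abstract. If 24 participants are meant to enter, say that invitations continue until 24 are randomised.

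The cost is protocol and analysis-plan wording, slightly more analysis work, possibly a few more invitations, and reliance on missing-at-random, which should be stated. The number recruited according to the abstract does not rise.

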#### Confidentiality

Each participant will be assigned an identification code to ensure anonymity throughout the research. Information that could potentially identify participants will not be disclosed at any point. Access to the collected, processed, and analyzed data will be restricted to the responsible researcher and his team exclusively. The data will be utilized solely for academic research purposes, and dissemination will take place through conferences and scientific articles.

### Strategies to increase intervention adherence

Assessors will maintain weekly communication with participants, either through telephone contact or in person, to gather feedback and address any potential discomfort related to the intervention. Furthermore, interventions will be scheduled based on the participants’ availability to ensure their engagement and maintain continuity throughout the intervention.

### Randomization and blinding

The order of intervention sessions will be randomized and counterbalanced across participants in a 1:1:1:1 ratio using an online random number generator (www.randomization.com). A member of the research team, not involved in the experimental procedures, will conduct the randomization, and maintain allocation confidentiality until the session begins. Two strategies will be implemented to ensure study blinding: i) participants will be unaware of the type of stimulation applied in each session and ii) the team member conducting the AE and tDCS sessions will not participate in the pre-and post-assessments.

### Assessments

#### Clinical and cognition

The motor severity of Parkinson’s disease, the stage of disease, and cognitive screening will be assessed by the Movement Disorders Society—Unified Parkinson’s Disease Rating Scale motor part (MDS-UPDRS III) [41], the adapted H&Y scale [39], and the MMSE [40], respectively. An experienced and trained evaluator will perform these assessments. The fear of falls and freezing of gait will be assessed by the Falls Efficacy Scale—International [42] and Freezing of Gait Questionnaire [43], respectively.

#### Gait and cortical activity while walking

Initially, trained evaluators will mark the Cz and Fpz positions on the participant’s head, corresponding to the 10–20 electroencephalography (EEG) system. The Cz position will be determined as the midpoint between the nasion and inion, and the pre-auricular points. The Fpz position will be marked approximately 13.5 cm below Cz, towards the forehead. These markings will serve as a guide for positioning a Neoprene cap, equipped with fNIRS optodes, on the participant’s head to record PFC activity during walking. The fNIRS optodes will be placed on the frontal part of the head, corresponding to Brodmann areas 9, 10, and 46 of both the left and right hemispheres, representing the dorsolateral and anterior PFC [15, 44, 45]. A tri-axial accelerometer will be positioned over the fifth lumbar vertebra of the participant to obtain gait parameters. The lumbar height will be individualized for each participant, recorded, and replicated in all assessments. After the preparations, participants will walk on a 26.8 m long circuit at a normal and comfortable pace for three experimental conditions: i) usual walking; ii) obstacle avoidance, and iii) with a cognitive dual task. Three trials will be conducted for each condition randomly, and the order of conditions will be identical in pre- and post-assessments. Each trial’s total duration will be 60 s (30 s standing and 30 s walking). During the standing still period (baseline), participants will be instructed to stand quietly, look straight ahead, and perform simple mental counting (addition of one by one). This task aims to standardize attentional demand during the baseline [46]. After a verbal signal (“ready, go”), the participant will perform the experimental task for 30 s. In the obstacle avoidance condition, four foam obstacles (60 cm long x 5 cm wide x 15 cm high) will be arranged along the circuit at a uniform distance between them [15, 45]. In the cognitive dual-task condition, an audio containing random numbers from 1 to 9 will play during the 30 s of walking. The participant must mentally count how many times a certain class of numbers (even or odd) was expressed [11, 45]. At the end of the pre-assessment, the fNIRS cap will be removed to carry out the intervention protocol, but appointments will be made to ensure the same positioning in the post-intervention assessment.

### Protocol of aerobic exercise combined with tDCS

Participants will be seated on a comfortable chair for tDCS preparations, blood pressure measurement, and resting heart rate. tDCS will be delivered by a MicroEstim Genius and/or MicroEstim Foco Research stimulator (NKL Electronic Products Ltda.—EEP, Brusque/Santa Catarina, Brazil) through conductive-rubber electrodes, placed in saline-soaked sponges (35 cm^2^, current density = 0.057 mA/cm^2^). The stimulation will target different regions in each session: active tDCS on M1, PFC, or multitarget, and a sham condition (Fig 2A). For multitarget, tDCS, two stimulators will be used, and the cathodal cable of the equipment will be linked to an inverted Y splice (NKL Electronic Products Ltda.—EEP, Brusque/Santa Catarina, Brazil) connected to the cathode electrode. In all sessions, anodal electrodes will be positioned according to the 10–20 EEG system, on M1 (C3/C4) and PFC (F3/F4), while the cathodal electrode will be positioned over the contralateral supraorbital region (FP1/FP2). Anodal stimulations will be applied to the cerebral hemisphere contralateral to the body side most affected by Parkinson’s disease, determined by MDS-UPDRS III items (3.3b-3.17d). The placement of three electrodes in all sessions will enhance participant blinding, making it more challenging to deduce the region and type (active or sham) of the stimulation being performed. Active tDCS stimulations (2 mA) will be delivered for 20 min, with a 30-seconds ramp-up at the beginning and a 30-seconds ramp-down at the end of the stimulation period (Fig 2B). For sham stimulation, the same 30-seconds of ramp-up and ramp-down will be applied, but the active stimulation will last only 10 s (Fig 2B). The stimulator will remain off for the next 19 min and 50 s.

**Fig 2 pone.0300243.g002:**
[figure not shown]
Experimental setup. A: tDCS electrode montages with three electrodes in all sessions. B: tDCS protocols for active and sham sessions. C: Protocol of aerobic exercise on treadmill.

AE will be conducted on a Millenium ATL treadmill (Inbramed—Brazilian Medical Equipment Industry Ltda., Porto Alegre/Rio Grande do Sul, Brazil). The intensity of exercise will be personalized for each participant and controlled by the percentage of their maximum heart rate (HRmax). Continuous monitoring and recording of the heart rate will be carried out using the Polar V800 (Polar Electro Brazil Commerce, Distribution, Importation, and Exportation Ltda., São Paulo/SP, Brazil). HRmax of each participant will be estimated using Eq 1, which has been previously validated [47]. The Eq 2 will be applied specifically for participants using β-blocker medication [48].
HRmax=208-(Age×0.7)
(1)
HRmax=164-(Age×0.7)
(2)

The exercise protocol will last 30 min and will consist of three parts: i) 5-minute warm-up phase (maintaining the HR between 50-60% of HRmax); ii) 20-minute exercise phase (maintaining HR between 60-70% of HRmax); and iii) 5-minute cooldown phase (maintaining HR below 50% of HRmax). tDCS will be applied during the 20-minute exercise phase and will be off in warm-up and cooldown phases (Fig 2C). The evaluator will increase and/or decrease the treadmill velocity to ensure that the percentage of HRmax remains within the specified target limits. The subjective perception of exertion (SPE) will be collected using the modified Borg scale (0–10 points) [49]. SPE will be recorded immediately before the exercise begins, every 5 min, and immediately after the end of the exercise. Additionally, other intervention outcomes will be recorded, such as treadmill velocity every 5 min and the total distance covered by the participant. For safety, all participants will be allowed to hold on to the handrails. A structured questionnaire will be administered immediately after the session to evaluate the potential side effects of tDCS [50, 51], and blood pressure will be measured again. At the end of the last intervention session, the evaluator will inquire with the participant about which session they received the sham condition. This approach will be implemented due to the extensive minimum interval between the first and last sessions (one month), making it challenging for participants to recall the sensations or discomforts experienced during each tDCS session.

